### Outcomes

The primary aim of objective 1 is to assess the impact of an SMI diagnosis on weight change. A pilot search of the database indicated waist circumference was not reliably recorded so we did not include this as a measure of adiposity. The outcome for objective 2 is change in cardio-metabolic risk factors for CVD, which include change in systolic and diastolic blood pressure, change in total cholesterol/high-density lipoprotein ratio, and change in glycaemia indicated by HbA1c or fasting glucose. The outcome for objective 3 is incidence of and mortality from CVD. The objective for 4 is coded weight management advice and referral to weight management services. We will interpret the data based on the associations for all outcomes, as well as consistency and interpretable patterns. The specific outcomes for each objective are outlined in table 1.

**Table 1 T1:** Outcome measures

Objective	Outcome	Measures
Objective 1: Examine the association between SMI and weight change	Weight change	Absolute mean weight change (kg)
		Percentage weight change (kg)
		Change in body mass index (kg/m^2^)
Objective 2: Examine the association between SMI and changes cardio-metabolic risk factors for CVD	Cardio-metabolic risk	Change in fasting blood glucose (FBG)
		Change in haemoglobin A1c (HbA1c)
		Change in mean total-cholesterol
		Change in triglycerides
		Change in low-density lipoprotein (LDL)
		Change in blood pressure (systolic (SBP) and diastolic (DBP))
Objective 3: Total incident and fatal CVD	Incidence of CVD and CVD fatalities	Angina diagnosed by GP
		Acute coronary syndrome
		Coronary heart disease
		Congestive heart failure
		Cardiomyopathy
		Total stroke
		Total fatal CVD events
Objective 4: Weight management advice and service referral	Proportion (%) of exposed and unexposed who are recorded as offered advice, and then offered and actually referred to a weight management service	

CVD, cardiovascular disease; GP, general practitioner; SMI, serious mental illness.

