### Confounding

We have identified confounding variables using directed acyclic graphs (DAGs), which aims to theoretically formalise potential confounders, colliders and biasing relationships.^26^ The DAG for each objective is described in online supplemental material S1. The DAG for objective 1 shows one direct path from the exposure (ie, SMI) to the outcome (ie, weight change), and four indirect paths: via health behaviours (ie, alcohol use, smoking and diet), SES status, psychotropic medication, and healthcare access and provision. Diet and physical activity are latent variables in CPRD Aurum because they are unmeasured. There are three confounding paths: via age, sex and ethnicity.^27 28^ Thus, the minimally sufficient adjustment for the total effect of SMI status on weight is to adjust for age, sex, and ethnicity.

10.1136/bmjopen-2021-053427.supp1Supplementary data

Frequency matching will ensure our ability to adjust for confounding variables that include age, sex, and calendar year, and matching on practice will remove practice-specific variables. In addition, we will fully adjust our models by considering several covariates in the relationship between the exposure and outcome (see table 2). All categorical variables will be analysed using the natural reference category as the reference group. Data on individual prescriptions for psychotropic and cardio-metabolic medications will be extracted from the primary care data from index date until censoring. For psychotropic medications, drugs will be classified according to the British National Formulary. For objectives 2 and 3, we will assess the impact of weight gain on change in cardio-metabolic risk factors and incidence of CVD using mediation analysis to allow us to estimate the direct (unmediated) and indirect (mediated) effects of SMI on CVD risk and incidence. To do this, we will fit two regression models: one regressing the outcome on the exposure, adjusting for confounders and another regressing the mediator on the exposure and confounders using the Stata *Med4way* command to estimate mediated effects.^29^ For objective 4, we will assess the presence of confounding by comparing estimates with and without adjustment. We will use Read codes, which have been previously developed by our team, to identify outcome and covariate records.

**Table 2 T2:** Confounders

Confounders and covariates		Measures

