Health behaviours	Smoking status	Categorical (0=never; 1=ex-smoker; 2=current smoker (light: 1–9 cigarettes/day; moderate: 10–19 cigarettes/day; heavy: 20+ cigarettes/day)). This is coded in GP records. We will use the most recent recorded value of smoking status at the study start date.
	Alcohol use	Continuous (units per week). This is coded in GP records. We will use the most recent recorded value of alcohol use at the study start date.
Demographics	Socioeconomic status (SES)*	Categorical (quintiles)
	Ethnicity†	Categorical (white; Asian or Asian British; black or black British; other ethnic group, mixed)
	Sex†	Binary (0=male; 1=female)
	Age at study entry, in years	Continuous
Physical and/or medical factors	Baseline weight status (body mass index (BMI))	Categorical (normal weight (BMI 18.5–24.9 kg/m^2^); overweight (25.0–29.9); obese (30.0–34.9); severe obesity (35.0–35.9); morbid obesity (40.0–44.9)
	Psychotropic medication	Categorical (antipsychotics (first-generation and second-generation); antidepressants; mood stabilisers)
	Cardio-metabolic medication	Categorical (blood glucose lowering medications; antihypertensive treatments, statins)
We include the following additional variables for objectives 3 and 4 only		
CVD risk factors	Total cholesterol/HDL ratio	Continuous
	Systolic and diastolic blood pressure	Continuous
	Glycaemia	HbA1c/fasting blood glucose (FBG)

*This variable is grouped according to practice level Index of Multiple Deprivation. This is an indicator of material deprivation based on income; employment; health deprivation and disability; education, skills and training; crime; barriers to housing and services; and living environment. It is categorised as quintiles 1–5 with 1 being the most deprived and 5 being the least deprived.

†This variable is grouped according to recommendations by the UK Office for National Statistics.^33 34^

CVD, cardiovascular disease; GP, general practitioner; HbA1c, haemoglobin A1c; HDL, high-density lipoprotein.

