#### Primary analyses

For objectives 1 and 2, the outcome will be visually inspected by plotting trajectories of weight and cardio-metabolic risk factor change using all repeated measurements for patients with SMI versus patients without SMI. For these analyses, we will use a mixed-effects linear regression model including terms for SMI, time and their interaction to estimate regression coefficients with 95% CIs by SMI status. Models incorporating psychotropic medications will analogously include medication-time multiplicative interaction terms. We will include a random effect for individual and practice identifier to account for intra-class correlation resulting from common practice membership. Diagnostic tests will be conducted to confirm linear regression assumptions are met including linearity of residuals, residual normality using quantile–quantile (Q–Q) plots, and residual heteroscedasticity using residual versus fitted value plots. We will assess for exploratory subgroup effects by adding interactions (eg, by age, sex, ethnicity and SES) and, if significant, we will assess the strength of the associations in separate subgroups for clarity. For objective 2, we will model the association between weight and cardio-metabolic change using restricted cubic splines to allow for non-linear associations. For objective 3, we will use Kaplan-Meier survival estimates for the exposed and unexposed groups to estimate the distribution of time from index date to total and fatal CVD and mortality (all-cause). The statistical equivalence of the two curves will be examined using the log-rank test. This analysis will use a survival from index date between the exposed and unexposed groups using an adjusted Cox proportional hazards regression model with follow-up time as the timescale. Restricted cubic splines will be computed with five knots to visually explore non-linear associations between the exposure and the outcomes. For objective 4, we will use a Poisson regression examining person-time to estimate the rate at which patients who received weight management services over the study period in patients with SMI compared with patients who do not have SMI, adjusting for confounders and BMI.

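### Objective 4 reads a change on adjustment as confounding, but the covariate list includes post-index treatment and SMI outcomes, so confounding and mediation cannot be separated

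*Protocol article*

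**What the plan says.** The rule for objective 4 is in the Confounding section: "For objective 4, we will assess the presence of confounding by comparing estimates with and without adjustment". The sentence does not say which covariates the adjustment covers.

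The same section describes the causal diagram for objective 1. It lists "four indirect paths: via health behaviours (ie, alcohol use, smoking and diet), SES status, psychotropic medication, and healthcare access and provision", then states: "There are three confounding paths: via age, sex and ethnicity". It concludes that "the minimally sufficient adjustment for the total effect of SMI status on weight is to adjust for age, sex, and ethnicity". It also says that a diagram for each objective is in supplement S1.

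On covariates, the section continues: "we will fully adjust our models by considering several covariates in the relationship between the exposure and outcome (see table 2"). Table 2 is titled as a table of confounders. It holds age, sex, ethnicity, SES, smoking, alcohol, baseline BMI category, psychotropic medication and cardio-metabolic medication. A later row reads "We include the following additional variables for objectives 3 and 4 only" and adds total cholesterol/HDL ratio, blood pressure and glycaemia. Prescriptions are collected between the index date and censoring.

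Under Primary analyses, the objective 4 Poisson model compares rates in patients with SMI "compared with patients who do not have SMI, adjusting for confounders and BMI".

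**The concern.** A change between a crude and an adjusted rate ratio shows confounding only when every added variable is a common cause of exposure and outcome, or stands in for one. If some are consequences of the exposure, the estimate also moves because part of the effect has been removed. The two kinds of movement look the same.

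Here the exposure is an SMI diagnosis, and treatment started after the diagnosis is the clearest case of a consequence. Objective 4 asks whether people with SMI are offered weight support as often as controls. Suppose they are referred more or less often because medication brings them into contact with the practice, or because their metabolic results prompt action. That is a real difference in care. Under the stated rule, its disappearance on adjustment could be written up as a confounded association.

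**Working it through.** The protocol gives no figure on this point. Its one computed design figure, the sample size of 3907, concerns CVD and does not enter. The check is first a reading of the text and then an illustration with assumed inputs.

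**1. Covariates against the protocol's own account**

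| Covariate in Table 2 | What the protocol says elsewhere |
|---|---|
| Age, sex | Named confounding paths (objective 1); also matched |
| Ethnicity | Named confounding path (objective 1); not matched |
| Smoking, alcohol | On an indirect path from SMI (objective 1), but recorded at study start |
| SES | On an indirect path from SMI (objective 1) |
| Psychotropic medication | On an indirect path from SMI (objective 1); collected after index |
| Cardio-metabolic medication | Collected after index |
| Cholesterol/HDL ratio, blood pressure, glycaemia | Added for objectives 3 and 4; the objective 2 outcomes include "change in systolic and diastolic blood pressure, change in total cholesterol/high-density lipoprotein ratio, and change in glycaemia indicated by HbA1c or fasting glucose" |
| BMI category | Baseline value; also named in the objective 4 model |

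Medication is the clear case, because it is measured after exposure. The CVD risk factors are a likely case, but Table 2 does not say when they are measured. Formal mediation analysis is planned for objectives 2 and 3 only, so nothing planned for objective 4 separates the two mechanisms.

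**2. Size of the shift with no confounding**

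Take one binary mediator M with prevalence p1 in SMI and p0 in controls, rate ratio RRm for the outcome, and direct SMI rate ratio 1. Then

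total RR = (1 + p1(RRm − 1)) / (1 + p0(RRm − 1)), and the RR adjusted for M is 1.00.

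All of p1, p0 and RRm are assumptions.

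- p1 = 0.5, p0 = 0.02, RRm = 1.1: 1.050/1.002 = 1.05
- p1 = 0.5, p0 = 0.02, RRm = 1.2: 1.100/1.004 = 1.10
- p1 = 0.7, p0 = 0.02, RRm = 1.2: 1.140/1.004 = 1.14
- p1 = 0.7, p0 = 0.02, RRm = 1.5: 1.350/1.010 = 1.34

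A higher control prevalence weakens the shift: p1 = 0.5, p0 = 0.25, RRm = 1.2 gives 1.100/1.050 = 1.05. A stronger mediator enlarges it: p1 = 0.8, p0 = 0.1, RRm = 2.0 gives 1.800/1.100 = 1.64. The fall to exactly 1.00 follows from setting the direct effect to 1.

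**3. Can the comparison tell the mechanisms apart?**

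One simulated Poisson cohort of 400,000 was run per setting, using the referral rate of 20 per 1000 person-years cited in the Introduction and the 3.2-year median follow-up from the sample size section. Assumed: a confounder C in 20%; SMI in 20%, or 35% of those with C where confounding is present; M in 60% of SMI and 15% of controls where mediation is present, otherwise 30% in both; rate ratio 1.5 for M, and 1.5 for C where confounding is present; direct SMI rate ratio 1.

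| Setting | Crude | Adjusted for C | Adjusted for C and M |
|---|---|---|---|
| Neither | 0.970 | 0.970 | 0.970 |
| Mediation only | 1.214 | 1.214 | 1.002 |
| Confounding only | 1.060 | 0.995 | 0.993 |
| Both | 1.267 | 1.195 | 0.985 |

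The first row, where the true value is 1, shows chance error of about 3%. Comparing only the first and last columns, mediation alone and confounding alone both end near 1. The middle column distinguishes them: adjusting for the true confounder leaves 1.214 unchanged under mediation alone, but removes the shift under confounding alone.

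**The case against.** Several points on the other side are fair.

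- **The diagram is borrowed.** The indirect paths and the age, sex and ethnicity set are stated for weight change. The objective 4 diagram is in S1 and not shown. This stands as a limit: paths to referral are partly inferred, and a charge that objective 4 abandons the diagram approach cannot be supported. It does not remove the point, because medication collected after the diagnosis is post-exposure whatever the outcome, and Table 2 itself assigns the CVD risk factors to objective 4.
- **The adjustment set is not spelled out.** The Poisson model names BMI beside the confounders, which may mean something narrower than all of Table 2. That is possible. But the table's title, the statement on full adjustment and the objective 4 row all point to the wide set, and the text does not rule it out.
- **No decision rule is given.** A reader might infer that the plan would declare confounding in a large share of analyses, for example by a 10% change rule. The protocol has no such threshold and no such step, so error rates calculated under one do not describe this plan.
- **The crude contrast stays visible.** A reader might infer that the total difference would be explained away. Table 1 reports proportions in both groups, and the comparison itself shows the unadjusted estimate. The risk lies in how the change is labelled.
- **BMI belongs in the model.** It is tempting to treat BMI as another consequence of SMI. Table 2 specifies baseline weight status, and the Introduction makes BMI the criterion for intervention, so comparing referral at equal BMI is a legitimate question. Removing it would change the planned estimand.
- **Age and sex may still matter.** Matching is at index, while exposed patients enter the subcohort on a BMI of at least 25 recorded at any time afterwards. Balance need not survive that selection, so it cannot be assumed that only ethnicity is left to confound.

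**Conclusion.** The point holds in a limited form. As written, the comparison for objective 4 cannot separate confounding from mediation, because the covariate list mixes pre-index characteristics with post-index medication and with risk factors whose changes are treated elsewhere as outcomes of SMI. A care difference operating through treatment or metabolic state could be called confounding. The documents do not support saying that the rule detects mediation as such: the change mixes both mechanisms, and real confounding, for instance by ethnicity, may contribute.

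The illustrated size is a total rate ratio of about 1.05 to 1.34 falling to 1.00 on adjustment, with larger values under stronger inputs. It rests on assumed mediator prevalences and rate ratios, a direct effect set to 1, and no confounding. It shows that the shift can be small or material, not what this study will find. Adjusted models remain useful; the fault is in the meaning attached to their difference from the crude estimate.

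**What to change.** Replace the objective 4 sentence in the Confounding section with wording such as:

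> In objective 4, confounding is judged by the change in the rate ratio when the confounders identified by the causal diagram and fixed at or before the index date (age, sex and ethnicity, together with the matching factors) are added. The primary rate ratio adjusts for these and for BMI, as already planned. Models that further add post-index medication and CVD risk factors are reported separately as explanatory. A change on adding them is not taken as evidence of confounding.

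The objective 4 diagram in S1 should be checked when this is done, so that SES, smoking and alcohol are placed according to it.

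The cost is one additional labelled model, and the fully adjusted rate ratio becomes secondary. No new data are needed, and BMI keeps its place in the primary model.

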### Data linkage

Data will be linked to the Hospital Episode Statistics (HES) and the Office for National Statistics mortality databases. Data linkage to the practice level Index of Multiple Deprivation (IMD), as a proxy measure for socioeconomic status (SES), will also be used when describing the baseline characteristics in the descriptive analyses and in secondary analyses.

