#### Study cohort

We will select a study cohort from the CPRD Aurum to investigate objectives 1–3. We will identify and extract the records in the primary care and HES dataset for all patients with a diagnosis of SMI (hereafter *exposed*) and who are eligible for data linkage. Diagnostic Read codes, which are the standard clinical codes used in UK general practice, will be used to identify an SMI diagnosis. We will also use codes according to the International Classification of Diseases version 10 (ICD-10) from the HES data. The date of the first SMI Read code will be used as the index date, which is the earliest date that an exposed patient may enter the study. From the study cohort, a subcohort of patients will be selected to investigate objective 4. To enter the subcohort, the exposed patient needs a recorded BMI ≥25 kg/m^2^ at any time after the index date. All information will be extracted for the period 01 January 1998 to 31 October 2020—the earliest and latest dates respectively that data are available.

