### Variable library

Exposures, outcomes and covariates of interest will be identified using medical coding (Read/SNOMED/EMIS), product coding (DM+D) and recording of patient death or transfer out of a participating practice in CPRD Aurum. The final definitions and code library has been drawn up and validated through consensus agreement among all investigators.

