Since the study is descriptive, any association observed would not imply an SMI diagnosis is causative of adverse physical health outcomes. However, we might assume the greater the magnitude of the observed association the less likely it is due to bias and more likely due to a causal process.^32^ Furthermore, diet and physical activity are unmeasured confounders because they are unobserved in CPRD Aurum. Similarly, other unmeasured confounders like poverty may place people with SMI at increased risk of homelessness, which has consequences on healthcare access and provision. We address this potential confounding by linking to patient level IMD as a proxy measure of SES, but acknowledge this may not fully capture deprivation and leaves room for residual confounding. Moreover, information bias may be present since the CPRD Aurum relies on a GP recording of health outcomes. Furthermore, we can only examine primary care prescriptions. Any prescribing solely within secondary care may not be included as this was not historically routinely recorded in GP records. Thus, it is possible we will miss the first prescription(s). Finally, physical health checks are not always performed on random samples of the population, and it is possible that more regular testing is done on people with overweight and obesity. We expect that some patients will have incomplete information recorded. However, by determining what proportion of patients do not have appropriate information recorded, we can evaluate the scale of these problems, and highlight the need for improved recording for continuity of care between healthcare professionals.

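### The stated outcome rule names only primary-care codes and Aurum death records, although HES and ONS data are linked and objective 3 needs incident and fatal CVD

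*Protocol article*

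**What the plan says.** Two places in the protocol article say how outcomes are found.

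- Confounding: "We will use Read codes, which have been previously developed by our team, to identify outcome and covariate records".
- Variable library, covering exposures, outcomes and covariates together: "medical coding (Read/SNOMED/EMIS), product coding (DM+D) and recording of patient death or transfer out of a participating practice in CPRD Aurum".

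Neither mentions ICD-10, HES or ONS. Elsewhere the article plans for more than this:

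- Data linkage: "Data will be linked to the Hospital Episode Statistics (HES) and the Office for National Statistics mortality databases". No use of either source for outcomes is given there.
- Study cohort: "We will identify and extract the records in the primary care and HES dataset for all patients with a diagnosis of SMI", followed by "We will also use codes according to the International Classification of Diseases version 10 (ICD-10) from the HES data". Both sentences belong to the paragraph that identifies the SMI diagnosis.
- Outcomes, Table 1: objective 3 lists acute coronary syndrome, total stroke and "Total fatal CVD events", among others. Only the angina row is tied to a GP diagnosis.
- Descriptive summaries: causes of death will be split into CVD and all-cause. The source of the cause is not named.
- Discussion: "information bias may be present since the CPRD Aurum relies on a GP recording of health outcomes".

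**The concern.** The outcome rule and the outcome list do not fit together. Acute coronary syndrome, stroke and CVD death often present in hospital or as death, and those are the records that the linked data hold. The article assigns hospital codes expressly to the exposure and says nothing equivalent for CVD. An analyst who followed the written rule would build the objective 3 endpoint from primary-care codes. A second analyst, reading the linkage section, would add HES and ONS. The two would count different events and date some of the shared ones differently.

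Under the first reading, CVD incidence is understated in both groups. If GPs code hospital events more or less completely for people with SMI than for matched controls, the hazard ratio is biased as well, and a large sample does not remove that.

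The point concerns how events after the index date are counted. It does not concern the index date or the baseline exclusions.

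**Working it through.** **1. The written rule applied to three records.**

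| Record | Found by the rule as written | Held in the linked data |
|---|---|---|
| A. Sudden coronary death, no earlier CVD code | A death; its cause is not supplied by either rule | ONS cause of death |
| B. Stroke admission and death in hospital, never coded by the GP | A death; no stroke | HES diagnosis, ONS cause of death |
| C. Myocardial infarction admission, coded by the GP months later or never | Event dated late, or missed | HES diagnosis at admission |

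Records B and C show the loss of incident events. Record A shows the gap for fatal CVD. The Statistical analysis section makes date of death both a possible outcome date and a censoring date. For fatal CVD only the cause of death separates the two, and no section names its source.

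**2. The plan's own sample size.** Inputs from Sample size calculation: CVD risk 3% in the unexposed, RR 1.3 (so 3.9% in the exposed), exposed-to-unexposed ratio 0.25, 80% power. Alpha is taken as 0.05 two-sided, which reproduces the printed figure.

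- Weighted mean risk: (0.039 + 4 × 0.03)/5 = 0.0318
- Null term: 1.960 × √(0.0318 × 0.9682 × 1.25) = 0.3845
- Alternative term: 0.8416 × √(0.039 × 0.961 + 0.03 × 0.97/4) = 0.1780
- n exposed = (0.3845 + 0.1780)² / 0.009² ≈ 3907

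This matches the stated 3907, as the number of exposed.

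**3. Equal under-capture (assumed; the documents give no capture rate).** Both risks are multiplied by the same capture fraction.

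| Capture in both groups | Exposed needed for 80% power | Power at 3907 exposed | Power at 135 870 exposed |
|---|---|---|---|
| 100% | 3907 | 80% | about 100% |
| 80% | 4918 | 71% | about 100% |
| 70% | 5640 | 65% | about 100% |
| 60% | 6603 | 59% | about 100% |
| 50% | 7950 | 52% | about 100% |

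The RR is unchanged, but reported incidence falls in proportion: at 80% capture, the assumed 1% per year would appear as 0.8%.

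**4. Unequal capture (assumed).** With rare events and no false positives, observed RR = true RR × (capture in exposed / capture in unexposed).

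- 70% v 75%: 1.30 × 0.70/0.75 = 1.21
- 65% v 75%: 1.30 × 0.65/0.75 = 1.13
- 75% v 70%: 1.30 × 0.75/0.70 = 1.39

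A gap of 5 percentage points in capture moves the RR by about 0.09 in either direction.

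**The case against.** The strongest reply is that neither rule is worded as exclusive. The Variable library list is demonstrably incomplete: it covers exposures and omits ICD-10, yet Study cohort uses HES ICD-10 codes for SMI. A list that does not exclude HES for exposures cannot be read as excluding it for outcomes. Further, the ONS linkage has no other apparent purpose than mortality, Descriptive summaries plans a CVD category for cause of death, Primary analyses plans time to fatal CVD, and Table 1 restricts only angina to a GP diagnosis, which would be redundant if every outcome were GP-coded. The Discussion sentence describes Aurum in a general limitations paragraph and is not an ascertainment rule. Finally, a journal article may leave code lists to a library that is not shown.

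Much of this stands. A reader might infer that the plan cannot count fatal CVD at all. The documents do not support that: they point to intended use of ONS cause of death. A reader might also infer a loss of power from the table above. That loss exists only at the 3907 minimum, not at the 135 870 SMI patients the feasibility work found.

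What does not stand is that nothing needs changing. The article does not merely omit the detail. It states an outcome rule twice, and names primary-care sources both times. Where it wanted HES codes, for SMI, it said so. Probable intent for ONS does not settle whether HES identifies and dates incident events, and it conflicts with the rule as written.

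**Conclusion.** The point holds as an inconsistency in how objective 3 events are ascertained. Followed as written, the rule misses or late-dates incident CVD recorded only in hospital or death data. It therefore understates incidence, and could bias the hazard ratio if GP coding differs by SMI status. The direction is unknown. For fatal CVD the source is probably ONS, but the stated rule contradicts that and must be brought into line.

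The size cannot be derived from the documents. The RR shifts to 1.21, 1.13 or 1.39 rest wholly on assumed capture rates and show sensitivity only. The case for acting rests on bias and understated rates, with no weight on power.

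**What to change.** Amend the outcome sentence in Confounding and the source list in Variable library so that they state, for objective 3:

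- a CVD event is the earliest of a GP code, a HES ICD-10 diagnosis or an ONS-registered CVD death;
- fatal CVD is taken from ONS cause of death;
- the angina outcome stays on GP codes, as Table 1 words it;
- follow-up ends no later than the end of linked-data coverage.

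The last item is a precaution. The article gives one extraction period, to 31 October 2020, for all information, and if the linked data reach that date nothing changes. The GP-only definition can be kept as an optional sensitivity analysis, which would show how much the source matters.

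The cost is wording and an ICD-10 code list for the CVD outcomes, with possibly slightly shorter follow-up. The linkage itself is already planned.
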